## Abstract

**Background:**

Dementia affects the mood of people with dementia but also of their caregivers. In the coming years, the number of people with dementia will increase worldwide and most of them will continue to live in the community as long as possible. Home-based psychosocial interventions reducing the depressive symptoms of both people with dementia and their caregivers in their own home are highly needed.

**Methods/Design:**

This manuscript describes the design of a Randomised Controlled Trial (RCT) of the effects of a home-based exercise and support programme for people with dementia and their caregivers. The aim is to randomly assign 156 dyads (caregiver and dementia diagnosed person) to an intervention group or a comparison group. The experimental group receives a home programme in which exercise and support for the people with dementia and their caregivers are combined and integrated. The comparison group receives a minimal intervention. Primary outcomes are physical health (people with dementia) and mood (people with dementia and caregivers). In addition, to get more insight in the working components of the intervention and the impact of the intervention on the relationship of the dyads a qualitative sub-study is carried out.

**Discussion:**

This study aims to contribute to an evidence-based treatment to reduce depressive symptoms among people with dementia and their caregivers independently living in the community.

**Trial Registration:**

The study has been registered at the Netherlands National Trial Register (NTR), which is connected to the International Clinical Trials Registry Platform of the WHO. Trial number: NTR1802.

## Background

Dementia affects the mood of people with dementia but also of their family caregivers [1,2]. Psychosocial interventions have been demonstrated to reduce caregiver distress and delay nursing home admission [3]. However, benefits of psychological interventions on caregiver's psychological mental health are limited especially with regard to caregivers' depressive symptoms [4-6]. Since the number of people with dementia is increasing worldwide, and most of them will continue to live in the community as long as possible, home-based psychosocial interventions reducing the depressive symptoms of both people with dementia and their caregivers in their own home are highly needed.

A review on combined programmes for people with dementia and their caregivers showed the effectiveness of four out of the 22 programmes for couples [7]. Two of these programmes showed significant beneficial effects on the depressive symptoms of persons with dementia as well as their caregivers: a short-term residential programme [8] and an active behavioral treatment developed by Teri [9]. Another intervention of Teri showed a reduction of depressive symptoms of people with dementia and an improvement of their physical functioning [10]. This intervention combines a physical exercise programme with teaching caregivers behavioral management techniques and to identify pleasant activities. The impact on caregivers' mental health was not measured in this study.

There is more research supporting the beneficial effects of physical exercise on the cognitive, physical and behavioural functioning of people with dementia [11-14]. Since physical exercise in combination with behavioral activation and pleasant activities seems to be promising and can be easily provided in the home of the people with dementia, an intervention programme like the one studied by Teri might have opportunities in other countries outside the US as well. Furthermore, it might have a beneficial effect on the relationship between persons with dementia and their caregivers. Since pre-caregiving and current relationship quality between care receiver and caregiver appear to have an impact on caregiver's wellbeing [15], this might be an additional advantage of such a combined intervention programme.

### Aim and main research questions

This study aims to develop an evidence-based treatment to reduce depressive symptoms among home living people with dementia and their caregivers. The feasibility and effectiveness of physical exercise and behavioural management and activation on depressive symptoms of both people with dementia and their caregivers will be investigated. A Randomised Controlled Trial (RCT) and a qualitative sub study are conducted to examine the effects of this programme. This article describes the protocol and discusses its benefits en limitations.

The main research questions are:

1. Is the home-based exercise and support programme feasible?

2. What is the effect of a home-based exercise and support programme on physical health, mood, cognitive functioning and behaviour of people with dementia?

3. What is the effect of the home-based exercise and support programme on general health, feelings of burden and mood of caregivers?

4. What are the working components of the intervention as perceived by the people with dementia and the caregivers?

5. What is the impact of this intervention on the quality of the relationship between the person with dementia and his/her caregiver?

## Methods/Design

### Participants

All dyads willing to participate in the study are eligible. Inclusion criteria for people with dementia are a diagnosis of dementia made by a physician (a general practitioner or a neurologist), minimum age 55 years, living at home with a caregiver willing to participate in the training sessions. Exclusion criteria concerning the people with dementia are the use of antidepressants, the presence of psychotic symptoms, Mini Mental State Examination (MMSE) score < 14 and receiving more than 2 days respite care in a day care facility.

Caregivers are spouses or adult relatives who live with the care receiver or spend a minimum of 4 hours every day with the person with dementia. Furthermore, caregivers should have a Centre for Epidemiologic Studies-Depression (CES-D) score > 5 and should have enough understanding of the Dutch language. Exclusion criteria for the caregivers are physical disorders that hamper assistance with the exercises, presence of psychotic symptoms and use of antidepressants.

### Sample size/Power

Sample sizes were calculated by a statistical power analysis. To detect an effect size of *d *> 0.40 between the two conditions with α = .05 and β = .80, 78 dyads in each group are needed.

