#### Statistical analysis

Data will be analyzed according to the intention-to-treat principle. Outcome analyses will compare the intervention group with the comparison group using regression analysis [47]. Baseline differences in demographic and clinical characteristics will be investigated using Chi-square tests, *t*-tests, and analysis of variance (ANOVA).

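### From the stated inputs, 78 dyads per group follows only from a one-sided 5% test; a two-sided test has about 70% power, not 80%, and the power is mislabelled as β

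*Protocol article*

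**What the plan says.** The Sample size/Power section of the protocol article is the only place that justifies the trial's size. It takes a standardised difference of 0.40 as the effect to detect and states, "between the two conditions with α = .05 and β = .80, 78 dyads in each group are needed". The Methods/Design part of the abstract gives the matching total: "The aim is to randomly assign 156 dyads (caregiver and dementia diagnosed person) to an intervention group or a comparison group".

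The article does not say whether the 5% level is one- or two-sided. The research question for people with dementia, under Aim and main research questions, is neutral in direction: "What is the effect of a home-based exercise and support programme on physical health, mood, cognitive functioning and behaviour of people with dementia"; the one for caregivers has the same form. The Statistical analysis section says, "Outcome analyses will compare the intervention group with the comparison group using regression analysis". No baseline correlation, gain from repeated measurements or allowance for dropout is given as an input to the calculation.

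**The concern.** The sentence has two faults.

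- **The label.** β is the probability of missing a true effect. Read literally, "with α = .05 and β = .80" describes a trial with 20% power.
- **The number.** With .80 read as power, 78 per group is well short of what a two-sided two-sample comparison at 5% needs for d = 0.40. It looks like the one-sided answer, yet no one-sided hypothesis is declared.

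This is the trial's only statement of power. If results are tested two-sided, as readers will assume, a null finding would be read as coming from an 80%-powered trial when the real power was lower. The mismatch also invites one-sided p-values later on, to agree with the calculation. That would double the chance of a false claim of benefit from 2.5% to 5%.

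**Working it through.** **Inputs.** d = 0.40, α = 0.05, .80 read as power and n = 78 per group all come from Sample size/Power. The total of 2 × 78 = 156, with equal groups, agrees with the abstract. Sidedness is not stated, so both readings are tried.

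**Formula (normal approximation).** n per group = 2(z_α + z_power)² / d², with z_power = 0.842 and d² = 0.16.

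1. *One-sided 5%:* 2(1.645 + 0.842)² / 0.16 = 77.3, so 78. The exact noncentral-t calculation gives 77.97, so 78. This reproduces the article's figure.
2. *Two-sided 5%:* 2(1.960 + 0.842)² / 0.16 = 98.1, so 99. The exact t calculation gives 99.08, so 100. That is 27–28% more than 78, or about 198–200 dyads in total.

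**Power with 78 per group at d = 0.40.** The standardised signal is d√(n/2) = 0.40 × √39 = 2.498.

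| Test at 5% | Normal approximation | Exact t |
|---|---|---|
| One-sided | Φ(2.498 − 1.645) = 0.803 | 0.800 |
| Two-sided | Φ(2.498 − 1.960) = 0.705 | 0.699 |

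The same comparison as a regression F-test (f² = 0.40²/4 = 0.04, N = 156) also gives 0.699. An unadjusted regression therefore changes nothing.

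**Smallest effect detectable with 80% power, two-sided, 78 per group.** (1.960 + 0.842) × √(2/78) = 0.449; exact t 0.451.

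**β = .80 taken literally (power 0.20, z = −0.842), two-sided.** 2(1.960 − 0.842)² / 0.16 = 15.6, so 16 (exact t about 16.5, so 17). This is nowhere near 78, so .80 must be the power.

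**Could another two-sided design give 78?** Adjusting for baseline multiplies the variance by 1 − r², where r is the baseline/follow-up correlation. The article gives no r, so a range is shown (normal approximation):

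| r (assumed) | n per group for 80% power | Power at 78 |
|---|---|---|
| 0.3 | 90 | 0.745 |
| 0.4 | 83 | 0.778 |
| 0.46 | 78 | 0.803 |
| 0.5 | 74 | 0.822 |
| 0.6 | 63 | 0.877 |

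Averaging two follow-ups multiplies the variance by (1 + ρ)/2, where ρ is the correlation between them. It gives 74 per group at ρ = 0.5, 79 at 0.6 and 84 at 0.7. An allowance for dropout only raises the number.

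**The case against.** The best defence is that the article names no test. It plans a regression and has a baseline and two follow-ups compared between groups. A two-sided baseline-adjusted analysis needs exactly 78 per group if the correlation is about 0.46, and at 0.5 the chance of missing d = 0.40 is about 18%, better than claimed. The article also never says its tests will be two-sided. Its aim is phrased as reducing depressive symptoms, and its Discussion expects benefit for both members of the dyad. Finally, a journal article condenses the full protocol, and the repair is one sentence.

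Part of this stands. That 78 arises only from a one-sided test is true of the stated inputs, not of every conceivable design, and the 30% miss rate belongs to an unadjusted two-sided test at exactly d = 0.40. The rest does not remove the problem. No correlation is given, and the unadjusted one-sided result (77.97) matches without any extra assumption, which makes it the likeliest origin. An aim or an expectation of benefit does not declare a one-sided test. Condensation can excuse an omitted detail, but here the published number depends on the detail. The β label is wrong on any reading.

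**Conclusion.** The concern holds. From the inputs the article states, 78 per group is the one-sided 5% answer. For a conventional two-sided, unadjusted comparison the trial has about 70% power at d = 0.40, or 80% power at d = 0.45; 80% at d = 0.40 would need 99–100 dyads per group. The stated β should read as power.

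This rests on reading .80 as power, on two equal groups of 78 with complete outcome data, and on no gain from covariates or repeated measurements, since none is stated. Missing outcomes would lower the power and baseline adjustment would raise it. Although the correction is small, it has to be made, because this is the trial's sole claim about its power.

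**What to change.** Rewrite the sentence under Sample size/Power so that it gives power = .80 (β = .20) and states the sidedness. Keep 156 dyads, and choose one of these on grounds that do not depend on the results:

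- **Restate the two-sided figures.** With 78 dyads per group, an unadjusted two-sided 5% test has 70% power for d = 0.40 and 80% power for d = 0.45.
- **Base the calculation on a baseline-adjusted regression.** Specify that adjustment in the Statistical analysis section, state the assumed baseline/follow-up correlation and its source, and show the range: about 74% power at 0.3, 78% at 0.4 and 82% at 0.5.

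Do not report one-sided p-values at 5% to fit the calculation. If one-sided testing really was the design, that must be declared and justified openly.

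The cost is one reworded sentence, plus a line on adjustment under the second option. No extra dyads are needed. Under the first option the stated power becomes less favourable.

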### Recruitment

Participants for this study are recruited throughout the Netherlands via caregiver centers, Alzheimer Cafés (easily accessible meetings for people with dementia, their caregivers and others) and by advertising in newspapers and via the Internet.

### Procedure

Trained master students in clinical psychology screen the interested dyads at intake. Eligible dyads are invited for baseline assessment and asked to sign an informed consent. When necessary, caregivers provide consent on behalf of the person with dementia. After the baseline assessment dyads are randomly allocated to the intervention or the comparison group. Within 2 weeks after the baseline measurement the intervention starts.

### Randomisation

After the baseline assessment dyads are randomly assigned by blocked randomisation (block size 20) to the intervention or comparison group. The allocation schedule is made by an independent researcher with a computer generated block randomisation. In this RCT dyads are aware of the treatment assigned. The examiners are blinded to the group allocation.

### Intervention group: combined home-based exercise and support programme

The intervention group receives a programme consisting of two parts: an exercise programme and a support programme. The goal of the exercise programme is to motivate dyads to complete 30 min of active exercise at least 3 days a week. There are four exercise components in the programme: flexibility, strengthening, balance and endurance. The activities should be fun and the person with dementia should enjoy performing them. The exercises are introduced gradually, session-by-session. The caregiver assists the person with dementia with the exercises at his/her level of physical abilities. Caregivers should watch carefully to prevent falls. If the person with dementia develops any sudden pain, shortness of breath, or ill feelings, exercises should be discontinued and a physician should be consulted. In addition, the goal of the support programme is to train caregivers in skills to communicate with the person with dementia and to stimulate implementation of pleasant activities in daily live. A coach visits the dyads in their own homes for 8 one-hour-long sessions during 3 months. The first month the dyads are visited weekly, followed by biweekly sessions over the next 8 weeks. The coaches are trained master students of the VU University at the Department of Clinical Psychology who follow a special training programme on geropsychology. During the study, all trained students receive minimal 3 times supervision of a psychologist specialized in working with older people.

For the present study, the intervention of Linda Teri has been translated into Dutch. The transfer from the American intervention to the Dutch design involved several adaptations to the Dutch care situation. The present intervention also includes elements of a Dutch exercise programme for people with dementia and their caregivers [16]. Materials like a ball, weights and elastics were added to make the exercises more attractive for people with dementia. Finally, in view of the implementation of the intervention in daily practice the intervention program needed to be shortened. The number of sessions has been decreased to eight (instead of the original 12) and, in addition, the frequency of the sessions in the first month to one instead of 2 sessions per week. According to the caregivers in the pilot study, the frequency and number of sessions were too high, consuming too much of their valuable time.

### Comparison group: minimal intervention

The comparison group receives a minimal intervention consisting of 1) special information bulletins with general information (like car driving, medication, night rest and domotica) monthly sent to the dyads; and 2) monthly phone calls by the coaches. The goal of these 10 min phone calls is to encourage staying active in everyday life and to keep social contacts and to discuss the daily routine. After 6 months the dyads in the comparison group are offered the opportunity to participate in the home-based exercise and support programme.

### Measurements

Measurements take place at baseline, at the end of the intervention after 3 months (post treatment) and at 6 months after baseline (follow up). For the intervention group only, there is a second follow up 12 months after baseline to examine whether effects are still present (Figure 1; Tables 1 and 2).

**Figure 1 F1:**
[figure not shown]
**Research procedure**.

**Table 1 T1:** Instruments at different assessment moments for people with dementia

Outcomes	Measurements	T0	T1	T2	T3
**PRIMARY OUTCOMES**					
Physical health	SF-36	x	x	x	x
	SIP	x	x	x	x

Depressive symptoms	MDS-DRS RAI HC	x	x	x	x
	Cornell	x	x	x	x
	GDS-15	x	x	x	x

**SECONDARY OUTCOMES**					
Behavioural problems	RMBPC problems	x	x	x	x

Cognition	GDS	x			
	MMSE	x	x	x	x
	ADS-AWT	x	x	x	x
	BADS-Key Search	x	x	x	x
	TMT A & B	x	x	x	x
	RBMT FR & PR	x	x	x	x
	GIT-Category Fluency	x	x	x	x
	Digit Span FW & BW	x	x	x	x

Rest/Activity	Actigraphy	x	x		

APOE4	ApoE4	x			

*SF*-36, Short Form Health Survey, *SIP *Sickness Impact Profile, *MDS-DRS RAI HC *Depression Rating Scale of the Resident assessment Instrument Home Care, *Cornell *Cornell Scale for Depression in Dementia, *GDS*-15 Geriatric Depression Scale 15, *RMBPC *Revised Memory and Bahaviour Problem Checklist, *GDS *Global Deterioration Scale, *MMSE *Mini Mental State Examination, *ADS-AWT *8 Words Test of the Amsterdam Dementia Screeningtest, *BADS-Key Search *Key Search Test of the Behavioural Assessment of the Dysexecutive Syndrome, *TMT A & B *Trailmaking Test A & B, *RBMT *Face Recognition & Picture Recognition of the Rivermead Behavioral Memory Test, *GIT-Category Fluency *Category Fluency from the Groninger Intelligence Test, *Digit Span FW & BW *Digit Span Test (forward and backward) of the Wechsler Memory Scale, *ApoE4 *Apolipoprotein E4

**Table 2 T2:** Instruments at different assessment moments for caregivers

Outcomes	Measurements	T0	T1	T2	T3
**PRIMARY OUTCOMES**					
Depressive symptoms	CES-D x	x	x	x	x

**SECONDARY OUTCOMES**					
General Health	GHQ	x	x	x	x

Burden	SPPIC	x	x	x	x
	RMBPC	x	x	x	x

Adrenocortical activity	Cortisol	x	x		

*CES-D *Centre for Epidemiologic Studies-Depression, *GHQ *General Health Question, *SPICC *Self-Perceived Pressure from Informal Care, *RMBPC *Revised Memory and Bahaviour Problem Checklist

### Instruments people with dementia

#### Primary outcome measures

##### Physical health and function

Two of the eight subscales of the Medical Outcome Study Short Form Health Survey (SF-36; [17,18]) are used to measure physical function and physical role functioning. Three subscales of the Sickness Impact Profile (SIP;[19,20]) are used to measure body care and movement, mobility and home management. Higher SF-36 scores indicate better health functioning; higher SIP scores indicate worse function. The caregiver completes both instruments.

##### Mood

The examiner completes the 19-item Cornell Scale for Depression in Dementia [21,22] together with the caregiver. The examiners are extensively trained and supervised by a psychologist to ensure interrater reliability. The Depression Rating Scale (DRS) of the Resident Assessment Instrument Home Care (RAI HC;[23-25]) is an observational scale consisting of seven items. Geriatric Depression Scale 15 (GDS 15) is used as a self-report measure [26,27]. Higher Cornell, DRS and GDS scores indicate greater impairment.

#### Secondary outcome measures

##### Behavioural problems

The Revised Memory and Behaviour Problem Checklist (RMBPC; [28,29]) is used to assess the level of behavioural disturbance of the person with dementia. The scale consists of 24 items reflecting three subscales, which measure the frequency of depressive behaviour, disruptive behaviour and memory related problems. Caregivers indicate how often problems occurred within the past week. Higher scores indicate greater disease severity.

##### Actigraphy rest/activity cycles

Rest activity data are collected by means of a wrist-worn, watch-size, ambulatory motion-detecting device, the Actigraph (Camebridge Neurotechnology Ltd., Camebridge, Great Britain). The Actigraph is set to record arm motion in 1-min epochs. People with dementia are asked to wear the Actigraph 24 h a day on their non-dominant wrist during 1 week. Data collected by Actigraph are related with rest-activity levels, an indirect measurement for sleep-wake cycles [30]. Interdaily Stability is a measure of the degree of resemblance between activity patterns of individual days. Higher values indicate a more stable rhythm. Intradaily Variability represents the fragmentation of periods of rest and activity. Normal rest-activity patterns show one major active period (day) and one major inactive period (night) and therefore show a low Intradaily Variability. Higher values indicate a more fragmented rhythm. Relative Amplitude represents the normalized difference between the most active 10-h period in the 24-h cycle in relation to the uninterrupted least active 5-h period. Higher values indicate a larger difference between daytime activity and night time rest and thus a stronger rhythm. The three rest-activity rhythm variables are converted into *z*-scores and combined to one Total Rest Activity Score.

##### Cognitive functioning

The *Global Deterioration Scale *(GDS; [31]) is used to clinically distinguish between the global stages from normality to severe dementia.

The *Mini Mental State Examination *(MMSE; [32,33]) is used to get an impression of global cognitive functioning.

The *8 Words Test *of the Amsterdam Dementia Screening Test 6 (ADS 6; [34]) is used to measure episodic anterograde memory.

To measure the ability to plan a strategy to solve a problem the *Key Search Test *of the Behavioural Assessment of the Dysexecutive Syndrome (BADS; [35]) is used.

*Trailmaking Test A & B *(TMT A & B; [36]) are used to measure visual conceptual and visuomotor tracking, flexibility and working memory.

The *Digit Span Test *(forward and backward) is part of the Wechsler Memory Scale-Revised (WMS-R; [37]). Work-memory is measured by digit span backward and short-term memory and attention is measured by digit span forward.

To measure visual long-term memory the *Face and Picture Recognition of the Rivermead Behavioural Memory Test *(RBMT; [38,39]) is used.

*Category Fluency *is a subtest from Amsterdam Dementia Screening Test 6 (ADS 6; [34]). This test requires a strategic search mechanism to retrieve information from semantic memory and is used to measure categorization abilities.

